## 50. Appendix 3 – EuroQol EQ-5D-5L

[figure not shown]

Effect of Remote Ischaemic Conditioning  
on clinical outcomes in ST segment elevation  
myocardial infarction patients undergoing  
Primary Percutaneous Coronary Intervention

[figure not shown]

### Health Questionnaire

### English version for the UK

ERIC-PPCI Trial Number:

E P 

|  |  |  |  |  |
|--|--|--|--|--|
|  |  |  |  |  |
|--|--|--|--|--|

Date of Birth:

|   |   |   |   |   |   |   |   |
|---|---|---|---|---|---|---|---|
| d | d | m | m | y | y | y | y |
|---|---|---|---|---|---|---|---|

# EQ-5D-5L

ERIC-PPCI Trial Number:

E

P

|  |  |  |  |  |
|--|--|--|--|--|
|  |  |  |  |  |
|--|--|--|--|--|

Date completed

|   |   |   |   |   |   |   |   |
|---|---|---|---|---|---|---|---|
| d | d | m | m | y | y | y | y |
|---|---|---|---|---|---|---|---|

Under each heading, please tick the **ONE** box that best describes your health **TODAY**

## Mobility

- I have no problems in walking about
- I have slight problems in walking about
- I have moderate problems in walking about
- I have severe problems in walking about
- I am unable to walk about

|  |
|--|
|  |
|  |
|  |
|  |
|  |

## Self-Care

- I have no problems washing or dressing myself
- I have slight problems washing or dressing myself
- I have moderate problems washing or dressing myself
- I have severe problems washing or dressing myself
- I am unable to wash or dress myself

|  |
|--|
|  |
|  |
|  |
|  |
|  |

## Usual Activities (e.g. work, study, housework, family or leisure activities)

- I have no problems doing my usual activities
- I have slight problems doing my usual activities
- I have moderate problems doing my usual activities
- I have severe problems doing my usual activities
- I am unable to do my usual activities

|  |
|--|
|  |
|  |
|  |
|  |
|  |

## Pain/Discomfort

- I have no pain or discomfort
- I have slight pain or discomfort
- I have moderate pain or discomfort
- I have severe pain or discomfort
- I have extreme pain or discomfort

|  |
|--|
|  |
|  |
|  |
|  |
|  |

## Anxiety / Depression

- I am not anxious or depressed
- I am slightly anxious or depressed
- I am moderately anxious or depressed
- I am severely anxious or depressed
- I am extremely anxious or depressed

|  |
|--|
|  |
|  |
|  |
|  |
|  |

# EQ-5D-5L

ERIC-PPCI Trial Number:

E P

- We would like to know how good or bad your health is TODAY.
- This scale is numbered from 0 to 100.
- 100 means the best health you can imagine.
- 0 means the worst health you could imagine.
- Mark an X on the scale to indicate how your health is TODAY.
- Now, please write the number you marked on the scale in the box below.

YOUR HEALTH TODAY =

The best health  
you can imagine

[figure not shown]

The worst health  
you can imagine

## Appendix 4: Additional Substudies

### Coronary Physiology substudy

#### Background and rationale

The assessment of the efficacy of reperfusion at the time of PPCI is challenging. Angiography and ST-resolution alone are good but imperfect indices. There is increasing data to support the use of coronary physiology indices measured at the time of PPCI as a surrogate index to measure the efficacy of reperfusion and provide insights into the effects on the microcirculation. Thus, the index of microcirculatory resistance (IMR) relates to biochemical and MRI infarct size, and an IMR value of >40 units (observed in about 1/3 PPCI patients) at the completion of PPCI is associated with adverse outcome. Recent intervention studies have adopted IMR as primary endpoint to test the effects of drugs or aspiration, although the clinical significance of this is uncertain. Our own group has been studying the changes in coronary physiology indices at the time of PPCI after aspiration and before coronary stenting. In addition we have used the opportunity to sample coronary sinus, aortic, culprit and venous blood for biomarker studies.

#### Hypothesis

1. RIC has beneficial effects on IMR at the completion of PPCI compared with control
2. RIC improves the response of the microcirculation at the time of PPCI to coronary stenting
3. IMR relates to CMR imaging indices in an interventional trial
4. Identification of circulating marker or effluent from the myocardium induced by RIC

#### Method

Coronary flow and pressure measurements are made using a coronary pressure/temperature sensitive guidewire, using established methods in routine use in clinical PCI procedures. The pressure wire is interchangeable with the coronary guide wire used in all PCI procedures, so is incorporated in to the procedure. Measurements that assess the integrity of the small blood vessels of the heart are made during the PPCI procedure, once the artery is opened and blood flow has been restored to the heart, and after implantation of a coronary stent Saline is flushed through the guide catheter to measure coronary flow using the transit time calculation. Adenosine is used as in standard clinical practice to increase blood flow. 

#### Sample Size

There are no published trials in this area and so sample size calculations have been based on similar patient groups and published literature: In the TIME trial mean IMR in an ACS cohort is 30 (SD 20). An effect size of 30% reduction in IMR is proposed, and allowing for dropout a sample size of 152 patients has been calculated at 80% power, 5% significance. The PATA STEMI study has an IMR reduction from 38U with a 26% effect size, and 128 patients. A study comparing aspiration and abciximab powered to show an almost 40% reduction in IMR from 34 to 20 calculated a sample size of 40. Published data suggest that the mean IMR after PPCI is 38 with an SD of 30. We would propose an effect size of 30% reduction in the treatment group and at 80% power with significance 5% the sample size would be 168 patients (84 per group). Allowing for dropout 180 patients will be required.

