### 30.2. Biomarker substudy to assess the effect of RIC on MI size (48 hr AUC)

A major secondary endpoint of the ERIC-PPCI study will be MI size as measured by 48 hr AUC high-sensitive Troponin T and CK-MB. To date the effect of RIC on this specific endpoint has not been investigated. Using 72 hr AUC Trop I, Thibault et al demonstrated that ischaemic postconditioning reduced MI size from 24.6 (SD 20.6) x10^4 to 13.0 (SD 7.0) x10^4 IU/L. This equates to a relative reduction in MI size of 47%. In order to demonstrate a more conservative 25% relative reduction in MI size with RIC in PPCI patients from 24.6 (SD 20.6) x10^4 using 48 hr AUC hsTrop T with 80% power and at the 5% significance level, will require 177 patients in each treatment group or 354 patients in total. Allowing for 10% dropout rate would require 400 patients in total.

In view of the clear positive skewness of the Troponin AUC it is anticipated that this outcome will be analysed on the log scale. This will lead to estimation of the relative reduction in the MI size, which is expected to be a more precise estimate of any treatment effect. Therefore, the planned sample size of 400 patients is likely to provide greater than 80% power and allow for larger than a 10% loss in outcomes due to incomplete Troponin AUCs.

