### 30.3. CMR substudy to assess the effect of RIC on MI size at 6 months

The CMR substudy primary endpoint is MI size (mass of late gadolinium enhancement) expressed as percentage of LV mass at 6 months. No clinical studies have previously used cardiac MRI to assess the effect of RIC on MI size. Using myocardial SPECT, [name] et al were unable to demonstrate a significant reduction in MI size at 30

days in all STEMI patients. Lonborg et al used CMR to demonstrate that ischaemic postconditioning reduced MI size at 3 months post-PPCI from 17±8% to 14±7% (mass of infarct expressed as a % of the LV mass). This equates to a relative reduction in MI size of 17.6% (equivalent to an absolute reduction of 3%). Based on this data, to demonstrate a similar relative reduction in MI size with RIC in PPCI patients from 17% (SD 8%) in the 6 month CMR scan, with 80% power and at the 5% significance level, will require approximately 112 patients in each treatment group or 224 patients in total. To allow for a 10% dropout rate we plan to recruit 250 patients in total.

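### The coronary physiology substudy's 84 per group gives about 69% power, not 80%, on the two-sided, common-SD basis used elsewhere in the protocol

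*Supplement*

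**What the plan says.** The Sample Size paragraph for the Coronary Physiology substudy (ERIC-PPCI protocol version 5.0, Appendix 4) reviews inputs from earlier studies and then settles on its own: "Published data suggest that the mean IMR after PPCI is 38 with an SD of 30". The target follows: "We would propose an effect size of 30% reduction in the treatment group". The result is that "at 80% power with significance 5% the sample size would be 168 patients (84 per group", and then: "Allowing for dropout 180 patients will be required". The paragraph does not say whether the test is one- or two-sided, which test is meant, what SD is expected in the treated arm, or what drop-out rate lies behind the step from 168 to 180.

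The same protocol sizes two other continuous outcomes, also at 80% power and 5% significance without naming sidedness. The biomarker calculation (section 30.2) "will require 177 patients in each treatment group or 354 patients in total". The CMR calculation (section 30.3) "will require approximately 112 patients in each treatment group or 224 patients in total". Section 41.2 plans differences in means with 95% confidence intervals for continuous variables. IMR is one of the listed secondary endpoints (section 29.2).

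**The concern.** A 30% reduction from 38 is 11.4 units, or 0.38 of an SD of 30. A standardised effect of that size usually needs clearly more than 84 per group for 80% power at two-sided 5%. If 5% significance means here what it means in the other calculations, the substudy has a 31% chance of missing its planned effect rather than 20%. A neutral IMR result would then be credited with more sensitivity than the design has. The primary endpoint and its sample size are not affected.

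**Working it through.** **Inputs.** Control mean 38, SD 30, 30% reduction, 80% power, 5% significance and 84 per group all come from the substudy's Sample Size paragraph. The difference is 0.30 × 38 = 11.4, which takes the treated mean to 26.6. Normal quantiles: 1.960 (two-sided 5%), 1.645 (one-sided 5%), 0.842 (80% power). The squared sums are (1.960 + 0.842)² = 7.849 and (1.645 + 0.842)² = 6.183.

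**What reproduces the stated 84?** With n per group = (SD₁² + SD₂²) × (squared sum) / 11.4²:

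| Assumption | n per group for 80% power | Power at 84 per group |
|---|---|---|
| Two-sided 5%, SD 30 in both arms | 2 × 900 × 7.849 / 129.96 = 108.7, so 109 (t-test 110) | 69.2% (t-test 68.7%) |
| One-sided 5%, SD 30 in both arms | 2 × 900 × 6.183 / 129.96 = 85.6, so 86 | 79.3% (t-test 79.0%) |
| Two-sided 5%, SD 30 and 21 (proportional to the mean) | (900 + 441) × 7.849 / 129.96 = 81.0 (Welch t-test 83) | 81.4% (Welch t-test 80.9%) |

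The second and third rows come close to 84. The first does not.

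**Power in the first row.** Standard error = 30 × √(2/84) = 4.629. Then 11.4 / 4.629 = 2.463, and 2.463 − 1.960 = 0.503, which gives 69.2%. If all 180 recruited patients were evaluable (90 per group), power would be 72.2% (t-test 71.7%).

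**Effect detectable with 80% power at 84 per group.** 2.802 × 4.629 = 12.97 units, and 12.97 / 38 = 34.1%.

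**Which basis does the protocol use elsewhere?**

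- Biomarker substudy: difference 0.25 × 24.6 = 6.15, SD 20.6. Two-sided with a common SD: 2 × 20.6² × 7.849 / 6.15² = 176.1, so 177, as stated. One-sided gives 139. The cited postconditioning study had a treated-arm SD of 7.0, and using 20.6 and 7.0 gives (424.36 + 49) × 7.849 / 37.82 = 98.2, so 99.
- CMR substudy: difference 3, SD 8. Two-sided with a common SD: 2 × 64 × 7.849 / 9 = 111.6, so 112, as stated. One-sided gives 88. Using the cited SDs of 8 and 7 gives (64 + 49) × 7.849 / 9 = 98.5, so 99.
- Primary endpoint (section 30.1): 8.5% against 6.375% (a 25% reduction) gives about 2393 per arm two-sided and about 1885 one-sided. The protocol states 2395.

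Both continuous-outcome calculations therefore use two-sided 5% and carry the control SD into both arms, even though each cites a smaller treated-arm SD. The planned 95% confidence intervals also correspond to a two-sided 5% test.

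**Log scale, for the optional part of the fix.** If IMR is log-normal with a constant coefficient of variation of 30/38 = 0.789, the log SD is √ln(1 + 0.789²) = 0.696. A 30% lower geometric mean is |ln 0.70| = 0.357. The standard error at 84 per group is 0.696 × √(2/84) = 0.107, the ratio is 3.32, and power is about 91%.

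**The case against.** The strongest reply is that 69% does not follow from the paragraph's stated inputs alone. It needs two additions, a two-sided test and an SD of 30 in the treated arm. SD 30 is quoted for patients with a mean of 38, not for a group lowered to 26.6. If the SD falls with the mean, a two-sided Welch test with 84 per group has 80.9% power, and the stated figure is sound. That assumption is not far-fetched: a log-normal IMR with a constant coefficient of variation, which is the basis for suggesting a log-scale analysis, implies it. The substudy hypothesis is also directional, so a one-sided test cannot be excluded from the wording.

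Much of this stands. A reader might infer that 84 is a proven arithmetic slip, or that a one-sided test must have been used. The documents support neither, because two different undeclared assumptions come close to 84.

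The reply does not make the stated power safe, however. Neither assumption is declared, and neither is used in the protocol's other calculations. A directional hypothesis settles little, since the main trial's hypothesis (section 28) is also directional and its calculation reproduces two-sided. A one-sided 5% test would also not match the planned 95% confidence intervals.

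It is also fair to say that a neutral result will be judged mainly by its confidence interval. That limits the consequence but does not make the power statement right.

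**Conclusion.** The point holds in a limited form. On the protocol's own basis (two-sided 5%, common SD of 30), 84 per group gives about 69% power for a 30% reduction. Reaching 80% needs 109 to 110 per group, and the reduction detectable with 80% power is about 34% (13 units). With a treated-arm SD proportional to the mean, two-sided power is about 81%, so the honest two-sided range is 69% to 81%, depending on an assumption that the paragraph leaves out.

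A reader might go on to infer a corrected recruitment target from these figures. The documents do not support a specific one: no drop-out rate is stated for this substudy, and the 6.7% implied by 168 and 180 (12/180) is only a back-calculation. The matter is confined to one secondary-endpoint substudy, but it concerns the figure on which that substudy's size rests.

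**What to change.** Restate the sentence in the substudy's Sample Size paragraph: with a two-sided 5% test and a common SD of 30, 168 evaluable patients give about 69% power for a 30% reduction in IMR, or 80% power for a 34% reduction. If a proportional SD was intended, say so, give the treated-arm SD (21 under proportionality), and report the 69% to 81% range. If a one-sided 5% test was intended, state and justify it, and reconcile it with the 95% confidence intervals in section 41.2.

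Optionally, pre-specify analysis of IMR on the log scale, as section 30.2 already anticipates for troponin AUC. The roughly 91% power this would give at 84 per group is conditional on IMR being log-normal with a constant coefficient of variation, and should be described that way.

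The cost is one corrected sentence, plus one line of analysis wording if the log scale is adopted. No extra patients are needed.

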#### Feasibility

Coronary physiology and IMR measures are practical and feasible in STEMI PPCI and we have extensive experience of these protocols in John Radcliffe Hospital Oxford as part of an ongoing OxAMI study, which is an observational cohort study. 

John Radcliffe Hospital, Oxford will be the lead centre. Additional selected sites will be invited to participate in this substudy.

# Thrombosis substudy

## Background

The pathogenesis of acute coronary syndromes (ACS) involves thrombosis on a background of plaque rupture and erosion, which can manifest in ST-elevation MI (STEMI). The risk of thrombosis is determined by the balance between the prothrombotic forces in blood and the capacity of the innate endogenous thrombolytic system to naturally dissolve any thrombus. Until recently, endogenous thrombolysis has been difficult to measure. Impaired thrombolytic status has been shown in NSTEMI, end-stage renal disease, stroke, and diabetes; and is increasingly recognised as a risk factor for arterial thrombosis. Effectiveness of endogenous thrombolysis is determined by thrombus properties (clot strength, determined by fibrin density, pore size and size of fibrin strands) and the rate of fibrinolysis, determined mainly by release of t-PA from the endothelium and PAI-1 from activated platelets. The exact mechanism through which ischaemic preconditioning improves outcomes in patients with STEMI is still not fully understood. In dogs, ischaemic preconditioning has been accompanied by down-regulation of platelet-fibrinogen binding and formation of neutrophil-platelet aggregates (1). In patients, platelet reactivity was reduced after repetitive, compared to single cycle exercise (2), whilst marked systemic platelet activation has been demonstrated in ACS (3) or acute limb ischemia (4). In patients undergoing radiofrequency ablation of atrial fibrillation, RIC reduced platelet activation and reactivity (5). In patients with subarachnoid hemorrhage, RIC prolonged the PT and INR (6). Activated platelets play an important role in the process of myocardial ischemia-reperfusion injury, and platelet-derived P-selectin is a critical mediator. In patients with coronary artery disease (7), RIC prior to exercise stress testing reduced ADP-stimulated platelet aggregation. However, the potential clinical benefit of any of these findings remains to be seen. Our pilot data on thrombotic status in PPCI: Data on 80 STEMI patients has yielded promising results. Rapid endogenous fibrinolysis was related to spontaneous STsegment resolution, TIMI 3 flow at presentation, and uneventful outcomes. Impaired endogenous lysis was associated with TIMI 0 flow and MACE within 30 days.

## Hypothesis

Platelet activation and impaired endogenous thrombolysis are critical determinants of outcome in patients with STEMI undergoing PPCI. RIC reduces ischaemic insult and improves outcome, and this is at least in part, through favourable effects on thrombotic status.

## Methods

All patients participating in ERIC-PPCI that are recruited at Lister Hospital, Stevenage will be enrolled.

## Blood samples

Venous blood samples (20ml) will be taken at presentation, 1 day post and 2-3 days post-STEMI and at the 6-8 week follow-up visit, for immediate point-of care thrombotic assessment, and the remainder will be stored in an accredited lab for later assessment of thrombogenesis and fibrinolysis. Samples will be taken by trained cath lab nurses and doctors already familiar with this protocol.

## Assessment of Thrombotic Status

Thrombotic status will be assessed using the point-of-care Global Thrombosis Test (GTT, Thromboquest Ltd., UK) and tests of thrombogenesis and fibrinolysis using micro-titre based assays on fresh frozen plasma (FFP). The GTT is a relatively novel point-of-care test, utilising native, nonanticoagulated whole blood, without external agonists, under high shear stress conditions, akin to that in a stenosed artery. It assesses platelet aggregation (time to occlusive thrombus formation; occlusion time (OT) and endogenous thrombolytic status (time to endogenous lysis of thrombus formed in the first phase of the test; lysis time(LT)) [10,11,21].

## Other Blood Tests

At each timepoint, a measurement of coagulation (fibrinogen, INR) and inflammation (high sensitivity C-reactive protein). Blood will also be spun and stored for future analysis as determined by study results.

## Follow-up

Follow up will be the same as the ERIC-PPCI protocol, however all 6-8 week follow-up will be conducted at the outpatient clinic.

## Handling of results

Patients receiving RIC or sham RIC, will be compared with respect to thrombotic status pre and post-PPCI, as well as the absolute change in thrombotic status pre and post intervention, and differences in ECG ST-resolution and clinical outcomes.

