### **Thrombosis substudy (all patients recruited at Lister Hospital)**

14. Thrombotic status pre and post-PPCI
15. Change in thrombotic status pre and post intervention
16. Differences in ECG ST-resolution and clinical outcomes

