### **41.2. Statistical analysis**

A detailed statistical analysis plan will be produced prior to unblinding of any data. The primary analysis will be a comparison of the cardiac death or HHF event rate one year after randomisation between the RIC and sham RIC arms of the trial amongst all STEMI patients. Hazard ratios and confidence intervals will be calculated using Cox proportional hazards modelling and Kaplan-Meier curves will be produced. In addition risk differences at one year will also be calculated together with 95% confidence intervals. The results for the individual components of the primary endpoint will also be presented together with other time to event secondary endpoints such as cardiac death or HHF at 30 days. Differences in means (continuous variables) together with 95% confidence intervals will be calculated using linear regression models and analysis of covariance techniques where appropriate. The primary analysis will be performed on an intention to treat basis i.e. by including all patients where possible according to the group to which they were randomised irrespective of whether they received the intervention as allocated. A secondary per protocol analysis will be undertaken including only patients who receive the allocated intervention as intended.

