### **41.4. Procedure to account for missing or spurious data**

All patients randomised to the trial will be analysed on an intention to treat basis. Data will be validated and the data analysis will take appropriate account of missing values. This process will be detailed in the statistical analysis plan.

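### The thrombosis substudy plans between-arm comparisons of values and absolute change without specifying baseline adjustment, although a presentation sample is planned for every substudy patient

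*Supplement*

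**What the plan says.** The analysis text for this substudy is one sentence in the ERIC-PPCI protocol version 5.0, Appendix 4, Thrombosis substudy, Handling of results. It begins "Patients receiving RIC or sham RIC, will be compared with respect to thrombotic status pre and post-PPCI" and continues "as well as the absolute change in thrombotic status pre and post intervention", before turning to ST-resolution and clinical outcomes. The list of secondary endpoints (section 29.2) gives the change its own entry, "Change in thrombotic status pre and post intervention", beside an entry for status before and after PPCI. Neither place names a model, a covariate or a main comparison.

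Under Blood samples, the same appendix says "Venous blood samples (20ml) will be taken at presentation", with further samples one day and two to three days later and at the 6-8 week visit. The thrombosis test yields an occlusion time and a lysis time.

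Two general rules bear on the point. Section 41.2 says that differences in means for continuous variables "will be calculated using linear regression models and analysis of covariance techniques where appropriate". Section 41.4 says "All patients randomised to the trial will be analysed on an intention to treat basis".

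The combined SAP version 3 details only the cardiac biomarkers substudy. It refers the reader to each trial's own SAP, and the ERIC-PPCI SAP is not in the supplement.

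**The concern.** An analyst who follows the appendix literally would compare raw values and raw changes between arms. Subtracting the baseline in full is the right adjustment only when the regression slope of follow-up on baseline is 1. For any smaller slope it over-corrects and adds noise. ANCOVA estimates the slope from the data.

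Precision matters here because the substudy draws on one hospital and states no sample size. The biomarker, CMR and coronary physiology substudies each have a sample size calculation.

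The sentence leaves two other things open. It compares the arms on the pre-PPCI value, which tells the reader nothing about treatment if the sample precedes the intervention. It also does not say which follow-up sample counts as post: three later samples and two test times give 3 × 2 = 6 follow-up values, none marked as the main one.

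**Working it through.** The plan gives no sample size, SD, effect size or power for this substudy, so there is no figure of its own to reproduce.

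**Inputs.** A presentation sample and three later samples (Appendix 4, Blood samples). The correlation r between baseline and follow-up is not given, so it is varied from 0.3 to 0.9 as an assumption. SDs before and after PPCI are first assumed equal.

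**Variances.** In units of the common variance, the three analyses have:

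- unadjusted change: 2(1 − r)
- ANCOVA: 1 − r²
- follow-up value alone: 1

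The ratio of change to ANCOVA is 2(1 − r)/[(1 − r)(1 + r)] = 2/(1 + r). The share of patients that ANCOVA saves for the same precision is 1 − (1 + r)/2 = (1 − r)/2.

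| r | Change | ANCOVA | Follow-up alone | Change / ANCOVA | Patients saved by ANCOVA |
|---|---|---|---|---|---|
| 0.3 | 1.40 | 0.91 | 1 | 1.54 | 35% |
| 0.5 | 1.00 | 0.75 | 1 | 1.33 | 25% |
| 0.7 | 0.60 | 0.51 | 1 | 1.18 | 15% |
| 0.9 | 0.20 | 0.19 | 1 | 1.05 | 5% |

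Change is less precise than the follow-up value alone when 2(1 − r) > 1, that is, when r < 0.5. A simulation with 93 patients and r = 0.5 gave a ratio of 1.35 against 1.33 in theory.

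**Unequal SDs.** With SDs s₀ before and s₁ after, the variance for change is s₀² + s₁² − 2r·s₀·s₁, and for ANCOVA s₁²(1 − r²). The difference is (s₀ − r·s₁)², which is never negative. The direction therefore does not depend on equal SDs, apart from the one degree of freedom spent on the covariate. The ratios in the table do depend on them.

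**Illustration.** Section 30.1 plans 2800 patients at 30 sites, on average 2800/30 ≈ 93 per site. Taking 93 for this hospital is an assumption; the documents give no figure for it. With 46.5 per arm, two-sided 5% and 80% power, the detectable difference in SD units is (1.96 + 0.84) × √(2v/46.5), where v is the variance in the first table.

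| r | Detectable, change | Detectable, ANCOVA | Power at 0.5 SD, change | Power at 0.5 SD, ANCOVA |
|---|---|---|---|---|
| 0.3 | 0.687 | 0.554 | 53% | 72% |
| 0.5 | 0.581 | 0.503 | 67% | 80% |
| 0.7 | 0.450 | 0.415 | 88% | 92% |
| 0.9 | 0.260 | 0.253 | above 99% | above 99% |

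For the follow-up value alone, the detectable difference is 0.581 and the power 67% at every r.

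**Timing of the first sample.** Three places need to be read together:

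- Appendix 4 puts the sample at presentation.
- The admission list in section 36.3 names the baseline test after the randomised intervention.
- The procedures table in section 36.1 marks the first thrombosis sample in the PPCI column at 0 hours, while randomisation and RIC or sham stand in the pre-PPCI column.

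A list order or a table column does not prove a sequence, but together these leave open whether the sample precedes the intervention.

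**The case against.** The appendix sentence names quantities, not tests. It compares follow-up values as well as change, so change is an addition and not a replacement. The general rule on "linear regression models and analysis of covariance techniques where appropriate" covers continuous outcomes and nothing in the appendix overrides it. If ANCOVA were applied to the change itself, the treatment effect and its standard error would equal those from ANCOVA of the follow-up value, with no loss at all. The ERIC-PPCI SAP, which might settle the model, is not shown. All of this stands. It limits the point to what the text leaves unspecified, and rules out saying that the plan has chosen raw change in place of baseline adjustment. It does not remove the point, because the substudy text itself does not say whether the general rule applies or which comparison is main.

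A reader might infer from the word receiving that patients will be grouped by the treatment they got. The documents do not support that. Section 33.2 speaks of patients being randomised to receive one or the other. Section 41.4 applies intention to treat to all randomised patients. Section 41.2 defines it for the primary analysis as "according to the group to which they were randomised irrespective of whether they received the intervention as allocated", and labels the treatment-received analysis separately as per protocol.

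It is also fair that adjusting for the presentation value is safe only if that sample precedes the intervention. This objection stands in full, and the remedy is made conditional on it.

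**Conclusion.** The point holds as a minor gap in specification. The substudy text plans comparisons of values and absolute change without specifying baseline adjustment, when the sample needed for it is already planned.

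That an unadjusted change score is no more precise than ANCOVA follows from the algebra, given a baseline unaffected by treatment and setting aside the one degree of freedom. The size rests on the unstated r and, for the tabulated ratios, on equal SDs: a variance 54% larger at r = 0.3, falling to 5% larger at r = 0.9. If r is high, little is lost. That the sample is small is likewise an inference, since no number is given.

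Nothing here bears on the trial's primary analysis, and an analysis by treatment received is not established.

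**What to change.** First, reconcile section 36.1, section 36.3 and Appendix 4 (Blood samples) on when the first thrombosis sample is taken, and confirm that the sample used as covariate precedes the start of RIC or sham. A sample taken after the start should not serve as a baseline covariate. It should not be subtracted either, since that could remove part of the effect.

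Then replace the comparison of status and change in Handling of results with wording such as: each post-PPCI occlusion time and lysis time, at each named time point, will be compared by randomised arm using ANCOVA with the pre-intervention value as covariate, on the log scale if skewed; change from baseline and the pre-intervention value will be reported descriptively.

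This agrees with sections 41.2 and 41.4. It costs one sentence and a timing clarification, and needs no new data if the planned presentation sample is confirmed to precede the intervention.
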